###### Sleep Quality

Sleep quality over the previous month will be assessed using the PSQI [24]. This questionnaire comprises 19 self-rated items that are grouped into 7 component scores: sleep quality, sleep latency, sleep duration, sleep efficiency, sleep disturbances, use of sleeping medication, and daytime dysfunction. Each component is scored from 0 to 3. The sum of these 7 component scores yields a global PSQI score ranging from 0 to 21, with higher scores indicating poorer sleep quality.

### Mental Health Status

Symptoms of anxiety and depression will be evaluated using the HADS. This scale consists of 14 items, divided into two subscales: Anxiety (HADS-A, 7 items) and Depression (HADS-D, 7 items). Each item is scored on a scale of 0 to 3. The scores for each subscale range from 0 to 21, with higher scores indicating more severe symptoms of anxiety or depression.

### Quality of Life

Health-related quality of life will be assessed using the SF-36 [25]. This instrument measures 8 domains of health status: physical functioning (PF), role limitations due to physical health (RP), bodily pain (BP), general health (GH), vitality (VT), social functioning (SF), role limitations due to emotional problems (RE), and mental health (MH). For each domain, item scores are coded, summed, and transformed onto a scale from 0 (worst possible health state) to 100 (best possible health state). This study will specifically focus on the PF and BP subscales to assess functional improvement. For the PF subscale used as a stratification factor, the 10 PF items will be summed as a raw score ranging from 10 to 30 and transformed using the formula PF = (raw score − 10)/20 × 100; therefore, possible PF scores occur in 5-point increments.

Additionally, the EQ-5D-3L will be used to evaluate health utility. It covers 5 dimensions: mobility, self-care, usual activities, pain or discomfort, and anxiety or depression. Each dimension has 3 levels: no problems, some problems, and extreme problems. The responses are converted into a single utility index using the Chinese population-based value set [26]. The scale also includes a EuroQol Visual Analogue Scale (EQ-VAS), where participants rate their overall health on a vertical scale from 0 (worst imaginable health) to 100 (best imaginable health).

### Global Impression

The Clinical Global Impression (CGI) scale will be used to assess the clinician’s global view of the patient’s illness and improvement [27]. It includes two subscales: Severity of Illness (CGI-S), rated on a 7-point scale from 1 (normal, not at all ill) to 7 (among the most extremely ill patients), and Global Improvement (CGI-I), rated from 1 (very much improved) to 7 (very much worse).

### Safety and Adverse Event Reporting

Adverse events (AEs) in this trial are defined as any untoward medical occurrence in a participant, regardless of its causal relationship with the treatment. Serious adverse events (SAEs) refer to events that result in death, are life-threatening, require hospitalization or prolonged hospitalization, or cause significant disability. AEs will be comprehensively monitored and recorded for both the intervention and control groups throughout the study. Specifically, monitoring will focus on intervention-related events such as subcutaneous hemorrhage (bruising), persistent local pain, skin abrasion, or fainting in the Tuina group, while simultaneously assessing potential side effects of concomitant medications or symptom fluctuation in the UC group. The number and type of AEs will be calculated, and patients will receive appropriate intervention if necessary. Any SAEs must be reported to the principal investigator and the Ethics Committee within 24 hours, and affected participants may be withdrawn from the study to ensure safety.

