## Methods

### Objective

The primary objective is to evaluate the efficacy of an 8-week standardized Tuina therapy plus usual care (UC) compared to UC alone in reducing fatigue severity in patients with CFS. Secondary objectives include assessing effects on the clinical response rate, sleep quality, mental health, quality of life, and clinical global impression, as well as evaluating the safety of the intervention and the long-term sustainability of therapeutic effects up to 24 weeks after treatment.

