### Trial Design

This study uses a prospective, multicenter, randomized, open-label, assessor-blinded, parallel-group design. The trial will be conducted at 6 clinical centers across China, with Shuguang Hospital affiliated to Shanghai University of Traditional Chinese Medicine serving as the leading center. The protocol has been developed in accordance with the SPIRIT (Standard Protocol Items: Recommendations for Interventional Trials) 2025 statement (Checklist 1) [17]. Table 1 outlines the major time points of this trial.

**Table 1. T1:** Schedule of enrollment, interventions, and assessments^a^.

Study period	Run-in	Allocation	Treatment	End of treatment	Follow-up	Follow-up	Other
Timepoint	Week −1 to 0	Week 0	Week 4	Week 8	Week 20	Week 32	Early withdrawal
Enrolment							
Informed consent	✓						
Eligibility screening	✓	✓					
Demographics	✓						
Medical history	✓						
Randomization		✓					
Interventions							
Tuina plus UC^b^			✓	✓			✓
UC			✓	✓			✓
Assessments							
CFQ-11^c^		✓	✓	✓	✓	✓	✓
SF-36 PF^d^	✓	✓	✓	✓	✓	✓	✓
SF-36 BP^e^		✓	✓	✓	✓	✓	✓
HADS^f^	✓	✓	✓	✓	✓	✓	✓
PSQI^g^		✓	✓	✓	✓	✓	✓
EQ-5D-3L		✓	✓	✓	✓	✓	✓
CGI^h^				✓			✓
Safety and other data							
Vital signs		✓	✓	✓			✓
Physical examination		✓	✓	✓			✓
Adverse events		✓	✓	✓	✓	✓	✓
Concomitant medications and therapies		✓	✓	✓	✓	✓	✓
UC log and consultation record		✓	✓	✓	✓	✓	✓
Adherence check			✓	✓			✓

a The “✓” symbol indicates that the item is scheduled at that time point.

b UC: usual care.

c CFQ-11: Chalder Fatigue Questionnaire.

d SF-36 PF: Short-Form 36 Physical Function Subscale.

e SF-36 BP: SF-36 Bodily Pain Subscale.

f HADS: Hospital Anxiety and Depression Scale.

g PSQI: Pittsburgh Sleep Quality Index.

h CGI: clinical global impression.

The study timeline is divided into three phases:

Run-in phase (day −7 to day 0): A 1-week screening period designed to confirm eligibility, ensure participant compliance, and collect stable baseline data (specifically depression levels and physical function) to serve as stratification factors for the subsequent randomization.Treatment phase (week 1 to week 8): Participants will receive the assigned intervention (Tuina plus UC or UC alone) for 8 consecutive weeks.Follow-up phase (week 9 to week 32): A 24-week posttreatment follow-up period to evaluate the long-term sustainability of the therapeutic effects.

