### Interventions

#### Control Group (UC)

Based on current guidance [1], participants in the control group will receive UC delivered by physicians experienced in CFS management. UC will include a baseline professional evaluation and structured education covering the nature of CFS, pacing and energy conservation, sleep hygiene, balanced diet, avoidance of overexertion and symptom-contingent activity escalation, and advice to avoid initiating Tuina, acupuncture, massage, or other traditional Chinese manual or physical therapies during the trial. This UC framework will be applied at all centers using the same written guidance document.

Symptom-directed treatment may be provided when clinically indicated for insomnia, pain, anxiety, depression, or other relevant symptoms. This may include prescription or nonprescription medications and individualized medical advice. Initiation or dose changes of medications and additional consultations will be permitted when clinically necessary, but the reason, drug name, dose, frequency, duration, and prescribing physician will be recorded in the electronic case report form. UC exposure will be recorded for both groups at each assessment visit using a structured UC log that captures medical advice, consultations, medications, self-management recommendations, and nonstudy therapies. Differences in UC exposure between the groups will be summarized, and sensitivity analyses may adjust for major concomitant medications or prohibited cointerventions if imbalances occur.

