### Data Analysis Plan

#### Analysis Populations

The primary efficacy analysis will be based on the modified intention-to-treat (mITT) population, operationalized as the full analysis set (FAS). The FAS will include all randomized participants with valid baseline CFQ-11 data who either receive at least 1 component of the allocated study management after randomization or provide at least 1 postbaseline CFQ-11 assessment. Study management refers to Tuina and/or usual care in the intervention group and usual care in the control group. Participants in the FAS will be analyzed according to their randomized allocation, irrespective of adherence, treatment discontinuation, number of completed sessions, protocol deviations, or concomitant care.

Participants who do not initiate any allocated postrandomization study management but provide valid postbaseline CFQ-11 data will remain in the FAS and will be analyzed according to randomized allocation. Postrandomization exclusions from the FAS will be limited to participants who withdraw consent for use of all data, have no valid baseline CFQ-11 data, are found after randomization to have a major eligibility error, or withdraw immediately after randomization before any study management and provide no postbaseline primary outcome data. All such exclusions will be documented before database lock and summarized in the participant flow diagram.

The per-protocol set (PPS) will include participants who complete at least 80% of the assigned intervention requirements, have week 8 primary outcome data, and have no major protocol violations. The safety set (SS) will include all randomized participants who receive at least 1 component of the allocated intervention or usual care and will be analyzed according to treatment actually received.

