### Missing Data

All missing data will be documented with reasons whenever possible and summarized by group and visit. No last-observation-carried-forward approach will be used. The primary MMRM analysis handles missing repeated outcome data through likelihood-based estimation under the missing-at-random assumption, using all available observed data. Multiple imputation by chained equations will be performed as a sensitivity analysis for the primary outcome and key secondary continuous outcomes when postbaseline data are missing. The imputation model will include treatment group, center, baseline stratification factors, baseline outcome values, observed postbaseline outcomes, demographic variables, and relevant UC or concomitant-treatment variables. At least 50 imputed datasets will be generated, and estimates will be combined using Rubin rules [28-30]. For the clinical response rate, response status will be derived from imputed CFQ-11 values in the MI sensitivity analysis; an additional conservative sensitivity analysis will classify participants with missing week 8 CFQ-11 data as nonresponders. If overall missingness exceeds 20% or differs between groups by more than 10 percentage points, additional sensitivity analyses using delta-adjusted pattern-mixture methods will be considered to assess departures from the missing-at-random assumption. Additionally, the robustness of the primary outcome will be assessed using the PPS population as a sensitivity analysis.

All statistical analyses will be performed using SAS version 9.4 (SAS Institute). Statistical significance is defined as a 2-sided *P*<.05.

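### The SAE rule permits withdrawal from the whole study, not only from study treatment, and so can cut short adverse-event and CFQ-11 follow-up to week 32 for little added protection

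*Protocol article*

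**What the plan says.** Safety and Adverse Event Reporting counts adverse events whatever their cause, and any hospitalization makes an event serious. SAEs go to the principal investigator and the Ethics Committee within 24 hours, and "affected participants may be withdrawn from the study to ensure safety". The same section also states that "AEs will be comprehensively monitored and recorded for both the intervention and control groups throughout the study".

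Other parts of the article bear on this:

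- The Objective section includes "evaluating the safety of the intervention and the long-term sustainability of therapeutic effects up to 24 weeks after treatment", and Trial Design describes "A 24-week posttreatment follow-up period to evaluate the long-term sustainability of the therapeutic effects".
- Table 1 schedules CFQ-11 and adverse events at weeks 4, 8, 20 and 32. It has one early-withdrawal column, which covers CFQ-11, adverse events and the other scales.
- Analysis Populations analyses the full analysis set as randomized, "irrespective of adherence, treatment discontinuation, number of completed sessions, protocol deviations, or concomitant care".
- Missing Data bases both the primary mixed model (MMRM) and multiple imputation on observed data. The mixed model is stated to rest on missing at random (MAR). For the responder outcome, "an additional conservative sensitivity analysis will classify participants with missing week 8 CFQ-11 data as nonresponders". Delta-adjusted methods will be considered "If overall missingness exceeds 20% or differs between groups by more than 10 percentage points".

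**The concern.** The rule removes the participant from the study when the safety purpose mainly calls for removing the exposure. In the usual-care arm, and in either arm after week 8, there is no Tuina left to stop. The remaining visits consist mostly of questionnaires, examinations and record-keeping, so leaving them protects the participant little. It does reduce visit burden, and it frees the participant from "advice to avoid initiating Tuina, acupuncture, massage, or other traditional Chinese manual or physical therapies during the trial".

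At stake first is the later course of participants who have had a serious event, whose safety follow-up matters most. Durability data to week 32 are lost with it. The second, smaller risk concerns the primary result and arises only from SAEs before week 8. Missing CFQ-11 values would then be tied to a bad event and could be worse than the model predicts from observed data.

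**Working it through.** **1. The texts side by side.** The SAE sentence names the study as what the participant leaves. The analysis-population text treats stopping treatment as something that can happen without leaving the analysis, and that analysis works best when outcomes are still collected after treatment stops. Nothing in the article keeps a participant withdrawn after an SAE in scheduled follow-up. The early-withdrawal assessment records status at exit only. Fatal SAEs are unaffected by the wording.

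**2. Follow-up lost per participant**, as (32 − week of withdrawal)/32:

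| Withdrawn at | Weeks lost (maximum) | Share of 32 weeks |
|---|---|---|
| Week 4 | 28 | 87.5% |
| Week 8 | 24 | 75% |
| Week 20 | 12 | 37.5% |

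**3. The plan's own figures.** Statistical Analysis gives a 3.0-point difference, SD 6.21, 90% power, two-sided 0.05, 92 per group, and 115 per group after 20% dropout. The pooled SD is √[(54 × 6.02² + 54 × 6.39²)/108] = 6.208. The noncentral-t calculation gives power 0.8999 at 91 and 0.9031 at 92 per group, so 92 is right, and 92/(1 − 0.20) = 115. The planned standard error of the difference is 6.21 × √(2/92) = 0.916.

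**4. Bias in the primary contrast.** The article gives no SAE rate, so these inputs are assumptions: 1–5% of one arm withdrawn before week 8 (0.01 × 115 = 1.2 to 0.05 × 115 = 5.8, about 1 to 6 people), with week 8 values 3–10 points worse than MAR predicts. Bias = (difference between arms in share withdrawn) × (departure from MAR).

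| Withdrawn (arm A vs B) | Departure | Bias | Share of 3.0 | In SE units |
|---|---|---|---|---|
| 1% vs 0% | 3 | 0.01 × 3 = 0.03 | 1% | 0.03 |
| 1% vs 0% | 10 | 0.01 × 10 = 0.10 | 3% | 0.11 |
| 5% vs 0% | 3 | 0.05 × 3 = 0.15 | 5% | 0.16 |
| 5% vs 0% | 10 | 0.05 × 10 = 0.50 | 17% | 0.55 |
| 5% vs 3% | 3 | 0.02 × 3 = 0.06 | 2% | 0.07 |
| 5% vs 3% | 10 | 0.02 × 10 = 0.20 | 7% | 0.22 |

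**5. Would the planned sensitivity analyses show it?** The nonresponder analysis always runs, but it covers the responder outcome only. Counting 1 to 6 of 115 as nonresponders moves that arm's rate by at most 1/115 = 0.9 to 6/115 = 5.2 percentage points. For the mean difference, the delta-adjusted triggers, counted as participants missing week 8, are:

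- more than 20% of 230, which is 46, so 47 participants; or
- a gap above 10 points: 11/115 = 9.6% and 12/115 = 10.4%, so 12 in one arm and none in the other.

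A few SAE withdrawals would reach neither by themselves.

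**6. Power.** If 0.5–5% were withdrawn on top of the planned 20% dropout (about 1 to 12 of 230), evaluable numbers would fall from 92 to between 91 and 86 per group, and power from 90.3% to between 90.0% and 88.3%. If they fall within the 20% allowance, power does not change.

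**The case against.** The strongest case against is that this is a preference rather than a defect. The sentence is permissive, and its stated safety purpose would discourage withdrawing someone whose event has nothing to do with the trial. It contradicts nothing outright: every trial loses some participants, and withdrawal after an SAE is not among the listed exclusions from the full analysis set. The article condenses a fuller protocol that may require SAE follow-up to resolution or data collection after treatment stops. The early-withdrawal assessment captures efficacy and safety at exit. The named Tuina-related events are mostly mild, and patients with severe or unstable disease are excluded, so SAEs may be rare. The upper bias of 0.50 points needs about six one-sided withdrawals before week 8, each 10 points (10/6.21 = 1.6 SD) worse than predicted. Seriously ill participants may miss visits under any wording.

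Most of this stands, and it limits the size of the point. The loss is possible, not certain; the exit assessment softens it; the follow-up percentages are maxima for one participant and say nothing about how many are affected. What does not stand is the appeal to the fuller protocol. The concern is with a rule the article states, not with a detail it leaves out, and that rule as written allows follow-up to end. The general purpose clause sets no limit by cause, arm or phase.

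**Conclusion.** The concern holds as a minor design point. The firm part is that the stated rule can truncate adverse-event, safety and durability data in participants selected for a serious event, against the plan's own aim of recording events to the end and judging effects up to 24 weeks after treatment. For an affected participant the loss is up to 75% of follow-up at week 8 and up to 88% at week 4. The number affected is unknown.

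The effect on the primary result is probably small: 0.03–0.50 points if losses are one-sided and 0.06–0.20 points for losses of 5% against 3%. Both ranges rest on the assumed withdrawal rates and departures from MAR, not on trial data. Loss in the Tuina arm would flatter Tuina, and loss in the usual-care arm would do the reverse. Loss of power is not a material concern.

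**What to change.** Reword the sentence in Safety and Adverse Event Reporting along these lines: after an SAE, study treatment may be discontinued by clinical decision; the CFQ-11 and adverse-event assessments scheduled in Table 1 continue to week 32 unless the participant declines or withdraws consent for follow-up.

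This keeps the clinician's freedom to stop Tuina, matches the analysis of participants as randomized whether or not treatment stops, and reduces missing data related to outcome. The cost is one sentence and a little more effort, for staff and participant, at visits already scheduled. A participant who finds the visits a burden can decline them. The sample size and the analysis model need no change.

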### Statistical Analysis

The sample size was determined based on the primary outcome, namely the change in CFQ-11 total score from baseline to week 8. The variability estimate was derived from individual-level data from an investigator-initiated, single-center pilot study conducted before the current multicenter protocol was finalized. In that pilot study, the mean reduction in CFQ-11 total score was 10.29 (SD 6.02) in the Tuina group and 5.36 (SD 6.39) in the control group. Because the primary end point of the present trial is change from baseline, the SDs of the baseline-to-posttreatment change scores were used for sample size planning. These values differ from the posttreatment group-level SDs reported in the pilot study table, which described the distribution of CFQ-11 scores at the posttreatment visit rather than the distribution of change scores. The pooled SD was calculated using the following formula:

$${SD}_{pooled}=\sqrt{\frac{(n_{1}-1)\times {{SD}_{1}}^{2}+(n_{2}-1)\times {{SD}_{2}}^{2}}{n_{1}+n_{2}-2}}$$

With n_1_=n_2_=55, SD_1_=6.02, and SD_2_=6.39, the pooled SD was as follows:

$${SD}_{pooled}=\sqrt{\frac{(55-1)\times 6.02^{2}+(55-1)\times 6.39^{2}}{55+55-2}}=6.21$$

The expected between-group difference was set at 3.0 points, corresponding to the prespecified clinically useful improvement threshold for CFQ-11 [23]. This conservative choice was made because the pilot study was single-center and relatively small, and pilot-based treatment effect estimates may be unstable or overestimate the effect expected in a larger multicenter trial. Using the MCID as the target effect ensures that the trial is powered to detect a clinically meaningful difference. To detect a 3.0-point between-group difference with a pooled SD of 6.21, 90% power, and a 2-sided significance level of 0.05, 92 participants per group are required. Allowing for a 20% dropout rate, the target sample size is 115 participants per group, for a total of 230 participants. The calculation was performed using PASS software.

### Data Analysis Plan

#### Analysis Populations

The primary efficacy analysis will be based on the modified intention-to-treat (mITT) population, operationalized as the full analysis set (FAS). The FAS will include all randomized participants with valid baseline CFQ-11 data who either receive at least 1 component of the allocated study management after randomization or provide at least 1 postbaseline CFQ-11 assessment. Study management refers to Tuina and/or usual care in the intervention group and usual care in the control group. Participants in the FAS will be analyzed according to their randomized allocation, irrespective of adherence, treatment discontinuation, number of completed sessions, protocol deviations, or concomitant care.

Participants who do not initiate any allocated postrandomization study management but provide valid postbaseline CFQ-11 data will remain in the FAS and will be analyzed according to randomized allocation. Postrandomization exclusions from the FAS will be limited to participants who withdraw consent for use of all data, have no valid baseline CFQ-11 data, are found after randomization to have a major eligibility error, or withdraw immediately after randomization before any study management and provide no postbaseline primary outcome data. All such exclusions will be documented before database lock and summarized in the participant flow diagram.

The per-protocol set (PPS) will include participants who complete at least 80% of the assigned intervention requirements, have week 8 primary outcome data, and have no major protocol violations. The safety set (SS) will include all randomized participants who receive at least 1 component of the allocated intervention or usual care and will be analyzed according to treatment actually received.

